### Assessments

2.5

Patients will be screened and enrolled at the Consultation and Psychosomatic Psychiatry Center of the University Hospital of Cagliari (San Giovanni di Dio Civil Hospital) and will be assessed before the treatment (t0), immediately post-intervention (t1), and after 6 (t2) and after 12 (t3) months post-intervention. The researchers responsible for measuring the outcomes will be three, and they will not be involved in the intervention phase. The following socio-demographic variables will be collected for each participant: gender and age; marital status; educational background; past and current occupational status; past and current organic physical illnesses; past and current mental health diagnoses; medications in use.

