### Data analyses

2.8

The statistical analysis will use SPSS software (version 21). Intra-rater and inter-rater reliability for the evaluation of the outcomes will be measured using Kappa statistics. Descriptive statistics for sociodemographic variables and the level of satisfaction of the experimental intervention, will be presented as frequencies (percentages) or mean ± standard deviation. To assess homogeneity between the experimental and control groups regarding “sex” and “age” distributions, chi-square tests and one-way ANOVA will be employed. A multivariate analysis, one for each considered outcome, will be conducted to compare means between the intervention and non-intervention groups over time (pre-and post-intervention), applying Bonferroni’s correction. The normality assumption of dependent variables will be assessed for sphericity, with Mauchly’s test use to verify the equality of variances among all combinations of related groups. Missing data will be considered incomplete and therefore excluded from the analysis.

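### The efficacy analysis leaves the role of the 6- and 12-month visits unclear, confuses normality with sphericity, and would gain some precision from baseline adjustment

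*Protocol article*

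**What the plan says.** Section 2.5 (Assessments) fixes four measurement times. Patients "will be assessed before the treatment (t0), immediately post-intervention (t1), and after 6 (t2) and after 12 (t3) months post-intervention".

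Section 2.8 (Data analyses) sets out the efficacy analysis in a few sentences:

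- Type of analysis: "A multivariate analysis, one for each considered outcome, will be conducted". It does not say whether this is a repeated-measures ANOVA, a MANOVA or a covariance analysis.
- Its purpose is to "compare means between the intervention and non-intervention groups over time (pre-and post-intervention), applying Bonferroni’s correction".
- Assumption check: "The normality assumption of dependent variables will be assessed for sphericity". The same sentence goes on to name Mauchly's test and describes it as checking that variances are equal across the related groups.
- Incomplete records: "Missing data will be considered incomplete and therefore excluded from the analysis".

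Section 2.1 makes feasibility the primary outcome and preliminary efficacy the secondary one. Section 2.9 gives a total of 30 participants and no allocation ratio.

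**The concern.** Three things in section 2.8 do not fit together.

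1. **Visits.** Four assessments are collected, but the comparison is described with two labels. If post means t1 alone, t2 and t3 have no stated analysis. If it means t1 to t3, the text does not say which comparison gives the efficacy result. The Introduction names persistence of results as a goal of cognitive remediation, and only t2 and t3 can show persistence.
2. **Assumption check.** Normality and sphericity are separate assumptions, and the sentence merges them. Under the two-time reading the named test is also empty, so the check conflicts with the comparison described just before it.
3. **Baseline.** Comparing means over pre and post makes the pre value one level of the time factor. With 30 participants, the precision that baseline adjustment would add is worth having.

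At stake is how useful the preliminary estimates will be for planning the confirmatory trial, which the Abstract gives as a purpose of this study.

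**Working it through.** The plan gives no figure to reproduce here: section 2.9 states 30 participants without a calculation.

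**Inputs.** From the documents: four assessment times (2.5), a pre/post comparison (2.8) and 30 participants in total (2.9). Assumed, because the documents give none: 15 per arm with no dropout, pre-post correlation r, the same SD at both times, and normally distributed scores.

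**Step 1: what Mauchly's test can do.** With k times there are p = k − 1 contrasts, and the test has p(p+1)/2 − 1 degrees of freedom.

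| Times k | p | Degrees of freedom |
|---|---|---|
| 2 | 1 | 1×2/2 − 1 = 0 |
| 3 | 2 | 2×3/2 − 1 = 2 |
| 4 | 3 | 3×4/2 − 1 = 5 |

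The statistic is W = det(S)/(tr(S)/p)^p, where S is the covariance matrix of the contrasts. At p = 1 numerator and denominator are the same number, so W = 1 whatever the data; a simulated data set confirmed this. At any k the test compares variances of differences between times and says nothing about the shape of the distribution.

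**Step 2: what the pre/post comparison amounts to.** In a two-group, two-time analysis the group-by-time test is the t-test on change scores. On a simulated data set F = 6.0239 and t² = 6.0239, with p = 0.0206 for both. In 20,000 simulated trials with no effect (15 per arm, r = 0.6), the type I error was 0.049 for the change score and 0.049 for baseline adjustment. Both are valid.

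**Step 3: precision.** Per-participant variance, in units of the outcome variance:

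- change score: 2(1 − r)
- baseline-adjusted: 1 − r²
- ratio: (1 + r)/2

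Adjusting for chance baseline imbalance has a small-sample cost, an expected variance factor of 1 + 1/(30 − 4) = 1 + 1/26 = 1.038, or 1.019 on the SE.

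| r (assumed) | SE ratio, large sample | SE ratio × 1.019 | Reduction in SE |
|---|---|---|---|
| 0.5 | 0.866 | 0.883 | about 12% |
| 0.6 | 0.894 | 0.911 | about 9% |
| 0.7 | 0.922 | 0.940 | about 6% |
| 0.8 | 0.949 | 0.967 | about 3% |

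**Step 4: confidence interval half-width at r = 0.6.**

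- Change score: 2.048 × √(2 × 0.8/15) = 0.669 SD
- Baseline-adjusted, before the small-sample cost: 2.052 × √(2 × 0.64/15) = 0.599 SD
- After that cost: 0.599 × 1.019 = 0.61 SD

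At r = 0.6 this is worth about 30/(0.8 × 1.038) = 36 participants analysed by change score, instead of 30.

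**The case against.** A reader might infer more than the text supports, in four ways.

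- **That t2 and t3 are certainly dropped.** Section 2.5 describes t1, t2 and t3 all as post-intervention, and section 2.3 uses a similar two-way label for the assessments as a whole. Mauchly's test has content only with three or more times, which also hints that more than two were meant. This stands: the fault is ambiguity, not proven omission.
- **That no visit-specific result will be produced.** The Bonferroni correction in the same sentence may refer to pairwise follow-up comparisons. This also stands, although the text does not say what is being corrected.
- **That Mauchly's test will be taken as proof of normality.** The second half of the sentence gives the test a variance role, and a fuller plan may contain a proper normality check. The wording still joins two unrelated assumptions, and added detail elsewhere would not correct it.
- **That the model is mis-specified because baseline is a response.** In a randomised trial this is valid when the group-by-time effect is tested, as the equal type I error shows. The cost is only precision. No model or covariates are named, and an article may leave covariates to the full plan, so adjustment is an improvement and not the correction of an error.

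Finally, efficacy is secondary, and section 4.1 defers its evaluation to larger studies. That limits the severity.

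**Conclusion.** The point holds as a should-fix. Two parts follow from the text alone: section 2.8 does not make clear which of the four assessments in section 2.5 enter the model, and its assumption check attaches a sphericity test to normality, a test that is empty if only pre and post are used. The third part is a recommendation. Its size at r = 0.6 is roughly 9% off the SE, and a half-width of about 0.61 instead of 0.67 SD. Over r = 0.5 to 0.8 the reduction runs from about 12% to about 3%. The correlation and the 15 per arm are assumptions, and dropout would widen both intervals. Nothing here affects the primary feasibility outcomes or makes the planned comparison invalid.

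**What to change.** In section 2.8, or in the full analysis plan:

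1. State which times enter the model. For each continuous outcome, fit a linear mixed model with t1, t2 and t3 as responses and arm, visit, arm-by-visit and baseline score as fixed effects. Age may be added but is optional.
2. Name the baseline-adjusted difference at t1 as the main preliminary estimate, and report the t2 and t3 differences to describe persistence. Say which comparisons the Bonferroni correction covers.
3. Replace the normality and Mauchly sentence with checks of model residuals, transforming skewed timed scores if needed.
4. Reword the missing-data sentence to match. If all four visits enter one complete-case analysis, a participant who misses only t3 could lose t0 to t2 as well. The mixed model keeps that participant's earlier visits, on the assumption that data are missing at random given what was observed.

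The cost is a few sentences of text and slightly more analysis work in the same software. No extra data are needed, since baseline and all later visits are already collected. Section 2.10 says recruitment was about to commence, so on the article's account the change could be made before outcome data are seen.

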## Introduction

1

As the global population continues to age, mild cognitive impairment (MCI) and dementia have become primary contributors to disability, particularly among the older adult population (1, 2). MCI delineates a transitional stage between the typical cognitive decline (CD) attributed to progressive aging and the initial phase of dementia (3, 4). Italy is the European country with the oldest population (23%), projections indicate that by the year 2050, one out of every five individuals in Italy will be in old age. This leads to a reduction in the working-age population and an increase in direct and indirect healthcare/social costs associated with the rising health problems (5). Risk factors such as physical, cognitive, and social inactivity are estimated to be responsible for about 40% of the risk of developing dementia over the lifespan (6). In general, approximately 50% of people with MCI progress to dementia within 3 years (7). Furthermore, CD is associated with depressive and anxiety symptoms and they both contribute to functional deterioration in daily tasks (7, 8). These conditions reduce the quality of life and the regulation of biological and social rhythms (9–11). Among others risk factors hypertension and cardiometabolic play a crucial role in the onset of cognitive dysfunction and progression to clinical over dementia (12). However, the pharmacological treatment and management of these conditions in older subjects is complex (13, 14) and may often result in worsening of cognitive progression (15). Growing attention has been given from researchers and from the European Union (EU) in recognizes the important goal of promoting research in the field of healthy aging, particularly non-pharmacological interventions aimed at preventing and/or delaying CD (16, 17).

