### Study design

2.1

This study is a feasibility randomized controlled (two-arm) clinical study protocol, adhering to the CONSORT flow diagram extension for feasibility study (37). The protocol is written according to the SPIRIT Standard Protocol Items (38). The RCT will involve individuals aged 65 and above with MCI. The experimental group will participate in a three-month CR program utilizing fully immersive VR, consisting of two sessions per week in addition to standard care. In contrast, the control group will receive only standard care. Consistent with the study outcomes (primary outcome of feasibility and secondary outcome of preliminary efficacy measurement), a randomized controlled design is essential even at the feasibility stage to ensure greater scientific rigor. For both outcomes, the variables will be assessed through comparison between the two groups.

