#### Primary outcomes

2.5.1

The primary outcome assesses the feasibility of the study, focusing on acceptability, tolerability (dropout rate), level of side effects and satisfaction. Variables in terms of acceptability, tolerability and satisfaction level will be assessed using an *ad-hoc* data sheet. Acceptability is measured as the proportion of recruited patients among those deemed eligible, while tolerability is assessed as the proportion of patients completing the trial intervention among those included.

The Italian adaptation of the Simulator Sickness Questionnaire (SSQ) will be used to record side-effects. The SSQ is a 16-item self-report questionnaire assessing the frequency of potential side effects related to the use of VR technologies, such as nausea, dizziness, headaches, eye fatigue, etc. (39).

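### Excluding missing data can bias the secondary efficacy comparison in either direction and wastes recorded data from a sample of 30

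*Protocol article*

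**What the plan says.** The missing-data rule is one sentence in section 2.8 (Data analyses) of the protocol article: "Missing data will be considered incomplete and therefore excluded from the analysis". The article sets no analysis population, all-available-data method or sensitivity analysis beside it.

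The same section plans one analysis per outcome to "compare means between the intervention and non-intervention groups over time (pre-and post-intervention"), with Bonferroni correction. It adds that "The normality assumption of dependent variables will be assessed for sphericity", using Mauchly's test. Section 2.5 schedules assessments at t0, t1 (end of intervention), t2 and t3 (6 and 12 months after the intervention).

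Section 2.5.1 describes the primary outcome as feasibility, "focusing on acceptability, tolerability (dropout rate), level of side effects and satisfaction". It defines one component so that "tolerability is assessed as the proportion of patients completing the trial intervention among those included". On side effects it says: "The Italian adaptation of the Simulator Sickness Questionnaire (SSQ) will be used to record side-effects". It does not say when the questionnaire is given. Section 2.1 adds: "For both outcomes, the variables will be assessed through comparison between the two groups". Section 2.9 gives 30 randomised participants.

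**The concern.** The exclusion rule is a choice that the article makes, not a detail it leaves open. An analysis plan that followed it would carry it forward.

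Two features of the trial make the rule risky. First, the arms differ in burden: one attends 24 supervised VR sessions over three months and the other has standard care only. Second, the protocol measures nausea, dizziness and similar effects because VR may cause them, and it treats drop-out as an outcome. Loss that differs by arm and relates to how participants fare is therefore foreseeable. Comparing only those with complete data would then no longer compare the groups as randomised.

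At stake are the preliminary effect estimates, which are meant to inform a confirmatory trial, and the side-effect and satisfaction summaries. With 30 participants, discarding scores already collected is also a cost in itself.

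**Working it through.** The article gives no expected drop-out, SD or effect size, so there is no stated figure to reproduce. All rates below are assumptions used to show size.

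**1. Does the rule remove people or only values?** The sentence speaks of data. Sphericity is a condition of repeated-measures ANOVA, and that method needs a complete row per participant. One missing modelled visit therefore removes the participant for that outcome. Mauchly's test is informative only with three or more time points, which suggests that follow-up visits enter the model, although the text in brackets names only pre and post.

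**2. How many remain if t0 to t3 are all modelled?** With t0 complete and independent missingness m at each of t1, t2 and t3, the expected number is 30 × (1 − m)³:
- m = 5%: 30 × 0.857 = 25.7, about 26
- m = 10%: 30 × 0.729 = 21.9, about 22
- m = 20%: 30 × 0.512 = 15.4, about 15

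If only t0 and t1 are modelled the loss is smaller: 30 × 0.9 = 27 at m = 10%.

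**3. How far can the pre-post contrast move?** Assume no true effect, full follow-up in controls, 25% drop-out in the VR arm, a t0-t1 correlation of 0.7, unit SD at both times, and drop-out log-odds rising by 1.5 per SD as the driving variable gets worse. By simulation, the completers' mean of the driving variable shifts by 0.277 of its own SD. The rest follows by arithmetic:
- *Driven by low t0 score:* t0 shifts +0.277 and t1 shifts 0.7 × 0.277 = +0.194. Change = 0.194 − 0.277 = **−0.08 SD**.
- *Driven by low t1 score:* t1 shifts +0.277 and t0 shifts +0.194. Change = **+0.08 SD**.
- *Driven by worsening:* the SD of change is √(2 × (1 − 0.7)) = 0.775. Change = 0.277 × 0.775 = **+0.21 SD**.

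If drop-out is unrelated to outcome, the shift is zero.

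**4. How does this compare with chance error?** Assume 15 per arm, so that 15 × 0.75 = 11.25 VR participants remain. The standard error of the difference in change is 0.775 × √(1/11.25 + 1/15) = 0.31 SD. The shifts are smaller than this, but unlike chance error they do not average out.

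**5. What would adjusting for t0 achieve?** The adjusted shift is the t1 shift minus 0.7 times the t0 shift:
- Low t0: 0.194 − 0.7 × 0.277 = 0.00
- Low t1: 0.277 − 0.7 × 0.194 = 0.14
- Worsening (t1 +0.107, t0 −0.107): 0.107 + 0.7 × 0.107 = 0.18

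Using all t0 data removes the bias when drop-out depends on recorded scores. It does not when drop-out depends on the unseen outcome; in the low-t1 case the adjusted shift (0.14) exceeds the unadjusted one (0.08). A sensitivity analysis is needed for that reason.

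**6. What of side effects, if only completers are summarised?** Let 30% truly have relevant side effects, with drop-out d₁ among them and d₀ among the rest. The completers' proportion is 0.3(1 − d₁) / [0.3(1 − d₁) + 0.7(1 − d₀)]:
- d₁ = 30%, d₀ = 10%: 0.21 / 0.84 = 25%
- d₁ = 50%, d₀ = 10%: 0.15 / 0.78 = 19%
- both 20%: 0.24 / 0.80 = 30%, no distortion

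**The case against.** The strongest reply is that this is a feasibility trial. Its main quantities are recruitment and retention, and the rule distorts neither: tolerability is counted over all those included, and acceptability over all those eligible. Efficacy is secondary, and the Discussion defers it to larger studies. This stands, and it limits the severity.

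Three stronger readings are tempting, and the document does not support them.

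- *That the results are biased, and in favour of VR.* Exclusion does no harm if data are missing completely at random, and the planned contrast can move either way. Quoting the shift in the raw t1 mean (about 0.2 SD in the low-t0 case) overlooks that the drop-outs' t0 scores are removed too, which turns the shift in change to −0.08 SD.
- *That dementia progression measures the loss.* The Introduction says that "approximately 50% of people with MCI progress to dementia within 3 years". At a constant hazard this gives 1 − 0.5^(15/36) = 25% by t3, or 7 to 8 of 30. These would be conversions, not missing assessments; nothing in the article withdraws converters.
- *That side effects will be understated.* This holds only if the scores of people who leave are absent or unused. The timing of the questionnaire is not stated, and scores taken during the sessions would survive the exclusion sentence.

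It is also fair to say that removal of whole participants is inferred from the method rather than written. It is nevertheless the natural reading, and nothing in the article softens it.

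**Conclusion.** The concern holds in a limited form. The exclusion rule, combined with the repeated-measures analysis that Mauchly's test implies, loses participants with a missed modelled visit. It leaves the secondary efficacy comparison open to bias of uncertain sign. Under the stated assumptions the size is about −0.1 to +0.2 SD in pre-post change. If four visits are modelled with 10% missing at each follow-up, about 22 of 30 participants remain.

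Side-effect and satisfaction summaries are at risk only if data recorded before drop-out go unused. The two feasibility proportions are sound. The point should be fixed, since the estimates are meant to guide a later trial, but it does not threaten the primary feasibility objective.

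**What to change.** Replace the exclusion sentence in section 2.8 with:

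> All randomised participants are analysed in their allocated group using all available assessments. Efficacy outcomes use a likelihood-based linear mixed model (SPSS MIXED) with t0 and all follow-up scores as repeated outcomes, so that no participant is deleted for a missed visit. Missingness and its reasons are reported by arm, with a simple sensitivity analysis for data not missing at random. SSQ and satisfaction are summarised from all data recorded for everyone with at least one VR exposure, including those who later drop out.

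The t0 score should enter as a repeated outcome, not only as a covariate. With t0 as a covariate, anyone without a later score still drops out of the model, and early VR leavers are the group of most interest.

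The cost is wording and slightly more analysis work. The planned software already contains the procedure, and the article says that recruitment had yet to begin.

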### Sample size considerations

2.9

In the registered clinical trial, our protocol outlined the recruitment and randomization of 30 eligible subjects in accordance with the predefined inclusion criteria.

### Trial status and ethical aspects

2.10

The study is registered on ClinicalTrials.gov (NCT06270966), and approval has been obtained from the Regional Ethical Committee (Protocol VR AND MCI n. 28,287–08/11/2023). Currently, the recruitment phase for the study is about to commence.

## Results

3

The results will concern the feasibility and preliminary clinical efficacy of a CR intervention using a fully immersive VR program for individuals with MCI. The trial results will be published in international peer-reviewed journals and disseminated at international congresses and meetings.

## Discussion

4

### Resource identification initiative

4.1

The primary objective of the trial is to comprehensively assess feasibility, particularly focusing on recruitment and retention rates. This evaluation provides essential insights for determining sample sizes in subsequent confirmatory trials. Additionally, to assess the side effect and satisfaction level of a VR-implemented CR tool, known as CEREBRUM. The secondary objective is to investigate cognitive and psychosocial variables. The hypothesis suggests that utilizing a CR with fully immersive VR program, with ecological instruments, can enhance cognitive abilities as well as other social and personal outcomes. The aim of this protocol study is to report the protocol of the trial, underlining methodological aspects in order to provide a response to the emerging health needs in line with the new evidences.

Indeed, the implementation of VR as a rehabilitative treatment in individuals with MCI is yielding positive results. Particularly, in a recent meta-analysis involving only people with MCI, a positive effect on clinical cognitive outcomes, specifically memory, language, and global cognition, was observed (29). However, few results are available regarding the improvement of clinical and functional outcomes due to the heterogeneity of variables and tools used, and the quality of the studies still need to improve (29, 53, 54). In general, the use of technological innovation and tools such as VR, based on the evidence described, can make the rehabilitation experience more engaging and facilitate the generalization of skills to real-life contexts, as the scenarios closely resemble those encountered in everyday life (54, 55). Naturally, technology should not replace the importance of the therapeutic relationship; rather, these are valuable tools that support rehabilitative techniques, with the relationship with the therapist remaining fundamental. Therefore, as in the intervention methodology used, exposure to VR is time-limited within each session.

Finally, for the present trial the purposed methodology uses a technological innovation tools that can more easily transfer the trained skills into the real world while always considering an approach based on the therapeutic relationship (31). The methodological approach employed in the trial reflects a person-centered and recovery-oriented approach to rehabilitation (29, 35, 36, 56), enabling participants to improve their skills and achieve an overall enhancement in their health and psychological wellbeing. Moreover, it aligns with the new framework for developing complex interventions where ensuring the reproducibility of interventions is a crucial methodological consideration (34, 57). Despite the methodological strength of the methodology, the present study is designed primarily as a feasibility study. Subsequent studies intending to evaluate efficacy and cost-effectiveness will require with a larger sample size. The findings of the trial will be deliberated among all the authors.
